## **2. STUDY OBJECTIVES**

### **2.1. PRIMARY OBJECTIVES AND HYPOTHESES AND ENDPOINTS**

To determine the benefits of different levels of support on the efficacy of an internet-delivered trans-diagnostic iCBT education program for anxiety and depression, using a 4-group CONSORT-R compliant, registered RCT.

The main hypotheses are that

1. Improvements will be observed at Primary Endpoint (post-education) in symptoms of anxiety and depression: Groups 4>3>2>1
2. Differences will be observed in the acceptability of the program: Groups 3>2>1
3. Differences will be observed in completion rates: Groups 3>2>1

The Primary Endpoint coincides with the post education questionnaires at week 9.

The Secondary Endpoint occurs at 3-month follow-up.

The Tertiary Endpoint occurs at 12-month follow-up.

## 2.2. SECONDARY OBJECTIVES

To identify variables likely to facilitate completion rates, satisfaction, and acceptability to consumers. To identify characteristics of people unlikely to benefit.

The results will inform us about who is likely to benefit from a trans-diagnostic education protocol and how best to administer this program in the future.

## 3. STUDY DESIGN

### 3.1. DESIGN

CONSORT-R compliant 4 parallel-group Randomised Controlled Trial

### 3.2. STUDY GROUPS

4 parallel groups (total sample size=350):

1. Waitlist control (n=50). Receive access to the program once the other groups have completed the program (week 9).
2. Self-guided (n=100). Receive immediate access to the program.
3. Self-guided + automatic emails (n=100). Receive immediate access to the program.
4. Self-guided + automatic emails + weekly telephone support (n=100). Receive immediate access to the program.

### 3.3. NUMBER OF PARTICIPANTS

350 in total: n=50 in Group 1, and 100 in Groups 2-4.

### 3.4. NUMBER OF CENTRES

1 – Clinical Research Unit for Anxiety and Depression, St Vincent's Hospital, Sydney

### 3.5. DURATION

1 February 2011 to 31 December 2012, inclusive of education, follow up and write up of results. The Primary Endpoint will be the end of active education for Groups 2-4 (who receive education immediately, i.e. 9 weeks after beginning the program), the Secondary Endpoint will be the 3 month follow up of these participants (i.e., 3 months after completion of education), and the Tertiary Endpoint will be the 12 month follow-up of these participants (i.e., 12 months after completion of education).

## 4. PARTICIPANT SELECTION

### 4.1. INCLUSION CRITERIA

1. Elevated symptoms of depression or anxiety as indicated by: Total scores on at least one of the following measures: PHQ-9 > 9; GAD-7 > 7; Mini SPIN > 5 [21]; ANSQ > 1 [22]. Scores above these cut-offs indicate likelihood of meeting diagnostic criteria for at least one of: depression, generalized anxiety disorder, social phobia, panic disorder, respectively.
2. Self-identifying as having difficulties with either depression, social phobia, panic disorder, or generalized anxiety disorder. Note that meeting diagnostic criteria for a formal anxiety disorder or depression is NOT an inclusion criteria – instead, participants need to have elevated symptoms of anxiety or depression as indicated in (1), above.
3. No current participation in cognitive behavioural treatment.
4. No change in medications in the period 1 month prior to this study, and no change in medications during the study.
5. Access to the Internet and a printer.

6. 18 years to 64 years old.
7. Resident of Australia.
8. Prepared to provide name, phone number and address, and to provide the name and address of a local general practitioner
9. Prepared to provide written informed consent.

4.2. EXCLUSION CRITERIA

1. Severe depression (score of 23 or greater on PHQ-9)
2. Suicidal intent or plan (either reporting suicidal intent or responding >2 to Question 9 [suicidal ideation] on the PHQ-9)
3. Scoring below cut-offs on the measures of anxiety and depression
4. Current substance abuse
5. Psychosis
6. Primary presenting problem not depression, generalized anxiety disorder, social phobia, or panic disorder.

## 5.STUDY OUTLINE

### 5.1. STUDY FLOW TABLE

| Date         | Stage                                                                                                               | Groups                                                                              |                                                                                                                             |                                                                                                                             |                                                                                                                             |
|---------------------|----------------------------------------------------------------------------------------------------------------------------|--------------------------------------------------------------------------------------------|-----------------------------------------------------------------------------------------------------------------------------|-----------------------------------------------------------------------------------------------------------------------------|-----------------------------------------------------------------------------------------------------------------------------|
| February-March 2011 | Recruitment                                                                                                                | Eligible applicants randomized to:                                                         |                                                                                                                             |                                                                                                                             |                                                                                                                             |
|                     |                                                                                                                            | Group 1
Waitlist
Control
(n=50)                                                   | Group 2
Self Guided
(n=100)                                                                                           | Group 3
Self Guided +
Auto Emails
(n=100)                                                                          | Group 4
Self Guided
+ Auto Emails
+ Weekly
Support
(n=100)                                                   |
| April 2011          | PRE-
EDUCATION
(administer
questionnaires
+ diagnostic
interview)                                           | Waitlist                                                                                   | Begin education                                                                                                             |                                                                                                                             |                                                                                                                             |
| April-May 2011      | EDUCATION                                                                                                                  | Waitlist                                                                                   | Receive education                                                                                                           |                                                                                                                             |                                                                                                                             |
| June 2011           | POST-
EDUCATION
Primary
Endpoint
(administer
post-education
questionnaires
+ diagnostic
interview) | Waitlist
(administer
questionnaires +
diagnostic
interview)
Begin education | POST-
EDUCATION
Primary
Endpoint
(administer post-
education
questionnaires +
diagnostic
interview) | POST-
EDUCATION
Primary
Endpoint
(administer post-
education
questionnaires +
diagnostic
interview) | POST-
EDUCATION
Primary
Endpoint
(administer post-
education
questionnaires +
diagnostic
interview) |
|                     |                                                                                                                            | Receive
education                                                                       | Follow-up period                                                                                                            |                                                                                                                             |                                                                                                                             |
| September 2011      | 3-MTH
FOLLOW-UP
Secondary
Endpoint
(administer
questionnaires)                                              | POST-
EDUCATION
(administer
questionnaires)                                       | 3-MTH FOLLOW-UP
Secondary Endpoint
(administer questionnaires)                                                        |                                                                                                                             |                                                                                                                             |
|                     |                                                                                                                            | Write up Results                                                                           |                                                                                                                             |                                                                                                                             |                                                                                                                             |
| June 2012           | 12-MTH
FOLLOW-UP
Tertiary
Endpoint
(administer
questionnaires
+ diagnostic
Interview)                 | No follow-up                                                                               | 12-MTH FOLLOW-UP
Tertiary Endpoint
(administer questionnaires + diagnostic Interview)                                 |                                                                                                                             |                                                                                                                             |
|                     |                                                                                                                            | Write up 12 month follow-up                                                                |                                                                                                                             |                                                                                                                             |                                                                                                                             |

## 5.2. INVESTIGATION PLAN

A CONSORT-R compliant, registered RCT comparing 4 parallel groups (total n = 350).

This design tests the relative benefits of different levels of support on symptoms of depression and anxiety and will help determine the acceptability of the program, and whether the education program is superior to natural remission. The 3 groups who immediately receive education (Groups 2, 3, & 4) will obtain different levels of support, compared to the fourth group (Group 1) a waitlist control (delayed education) group. As in any RCT accurate patient selection, good randomization, reliable and valid outcome measures, and low drop-out rates are critical. Analyses based on completers and on intention-to-treat will be performed.

Patients will be randomly allocated to one of the four groups (total n=350). Randomization will be done via [www.random.org](http://www.random.org) (using a sequence generated by an overseas colleague not associated with this research).

1. **Group 1: Waitlist control** (n=50). This group will receive access to the entire program + automatic emails once the other groups have completed the program (week 9).
2. **Group 2: Self-guided** (n=100). This group will receive immediate access to the entire program.
3. **Group 3: Self-guided + automatic emails** (n=100). This group will receive immediate access to the program + will receive regular automatic emails. These emails provide notification of when additional resources become available and help remind the participant about tasks to practice.
4. **Group 4: Self-guided + automatic emails + weekly telephone support** (n=100). This group receive immediate access to the program + regular automatic emails, and will also receive a brief weekly telephone call from one of the researchers. The aim of this weekly telephone contact is to reinforce progress, provide guidance about aspects of the program the participant may not be aware of, and to provide encouragement.

The education program is delivered via the website [www.virtualclinic.org.au](http://www.virtualclinic.org.au). The program consists of 5 online lessons conducted over an 8 week period, in which participants are encouraged to complete one lesson every 10 days. The program is comprised of the following lessons and the materials include key components of CBT for anxiety and depression:

1. *Lesson One:*
  - a. Learn about the physical, cognitive and behavioural symptoms of anxiety and depression
  - b. Learn about the principles of CBT
2. *Lesson 2:*
  - a. Learn about the relationship between the way you think and feel
  - b. Begin monitoring and challenging unhelpful thinking patterns
3. *Lesson 3:*
  - a. Learn about physical symptoms of anxiety and depression and managing these with de-arousal and activation techniques
  - b. Assertiveness skills
4. *Lesson 4:*
  - a. Learn about behaviours (low activity and avoidance) that make anxiety and depression worse, and how to challenge those behaviours
5. *Lesson 5:*
  - a) Learn about problem solving, relapse prevention and staying well

On application, applicants will complete screening measures of anxiety and depression. Those with scores too high or too low (asymptomatic) will not be eligible. Eligible applicants will be telephoned by

the researchers, who will conduct diagnostic interviews via telephone. Applicants who meet diagnostic criteria for a primary disorder other than those targeted by this education protocol will not be eligible but will be informed about other options for education or treatment.

At the beginning of the education program all participants will complete the outcome measure questionnaires. The questionnaires being administered in this study are all valid and reliable clinical and research measures.

All participants will complete a second entire set of questionnaires at the post-education point (Primary Endpoint) and will also be telephoned by the researchers who will conduct the telephone interviews again. Participants in Groups 2, 3 and 4 will also be asked to complete a shorter set of questionnaires at 3 and 12 months follow-up. Participants in Group 1 (Waitlist control group) will begin the program immediately after the other groups have completed the education.

In addition, brief measures of anxiety and depression (the GAD-7 and PHQ-9) will be administered at the beginning of each lesson to monitor anxiety and mood. We will also encourage feedback from participants at every stage of the project to determine how to improve the content and delivery of the program.

### 5.3. STUDY PROCEDURE RISKS

It is expected that adults with symptoms of depression and anxiety will experience clinically significant reductions in the severity of their symptoms. It is also hoped that the techniques taught in this program will be applied by participants after the trial is completed, resulting in long term improved management of symptoms of anxiety. However, because anxiety and depression often develop in teenage hood and early adulthood, it is likely that most of participants will have experienced distressing levels of emotions for several decades. The education protocol encourages them to learn and practice techniques for managing symptoms of anxiety and depression and, in the short term, this often leads to an increase in levels of anxiety.

Our priority is to support participants to stay safe. Risk management will occur at all stages of this project including:

#### At Application:

Applications with severe symptoms of depression (total score of >23 on the PHQ-9, a reliable and valid measure of the symptoms of depression), will not be eligible to participate, and will be provided with written contact details of how to access urgent support and will be strongly encouraged to do so. Applicants assessed as having a primary disorder not targeted by this program (as determined by diagnostic telephone interview) will not be eligible for this program, but will be informed about more appropriate iCBT program which target their specific problem, as well as being encouraged to consider other education and treatment options including accessing their GP or local services.

All applicants will also be screened for risk of suicide or self harm. Those at risk will not be eligible to participate, and will be provided with written contact details of how to access urgent support and will be strongly encouraged to do so.

All applicants will be informed (verbally and in writing) of steps to take if they feel emotionally distressed during the trial, including the contact details of the researchers, the importance of contacting their own GP, and contact details of emergency services. Applicants must also provide contact details for their GP, who we will only contact if we are sufficiently concerned about the participant (this is explained to participants verbally, and in the Participant Information Sheet). We do not contact GPs as a standard protocol, as many participants have said that they prefer their participation to remain confidential.

#### During the Trial:

All participants will be screened regularly for deterioration in mood or distress when they complete brief measures of anxiety and depression (prior to completing each new lesson). All electronic communications (emails) contain contact details for emergency services (in the footer), and written details about staying safe in mental health emergencies are included in several locations in the program materials.

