#### During Completion of Questionnaires:

Questionnaires of anxiety and mood will be completed at pre-education, prior to completing each new lesson, at post-education, at 3 month follow-up, and for Groups 2, 3, and 4, also at again at 12 month follow-up.

Any deterioration in mood or elevated distress will trigger protocols involving contacting the participant to discuss their emotional state, and a meeting between the Clinical Psychologist and Chief Investigator/other researchers to develop a management plan, which is then documented and followed up as per VirtualClinic policy.

Members of the research team will meet at least 2 X weekly to discuss progress of each participant and of the overall trial. The Chief Investigator will monitor overall progress weekly and will take overall responsibility for this trial. All communications with participants will be documented as per VirtualClinic documentation policies. All adverse events will be promptly reported to the HRECs and CRUfAD Director.

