#### 6.3. PARTICIPANT SAFETY

During the trial all participants will be screened before completing each lesson when they complete brief measures of anxiety and depression. All electronic communications (emails) contain contact details for emergency services (in the footer), and written details about staying safe in mental health emergencies are included in several locations in the program materials.

Questionnaires of anxiety and mood will be completed at pre-education, before each of the 5 lessons, and at 3-month and 12-month follow-up. Any deterioration in mood or elevated distress triggers protocols involving contacting the participant to discuss their emotional state, and a meeting between the Clinical Psychologist and Chief Investigator/Other researchers to develop a management plan, which is then documented and followed up as per VirtualClinic policy. Participant safety and wellbeing is the paramount consideration. Participants will be invited to contact the investigators at any time should their wellbeing deteriorate.

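### All participants are said to be screened for deterioration, but the screen is tied to lessons, so the waitlist group has no scheduled PHQ-9 or GAD-7 for about 63 days

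*Protocol*

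**What the plan says.** Two safety passages make the same statement about everyone in the trial. Section 5.3, under During the Trial, says "All participants will be screened regularly for deterioration in mood or distress when they complete brief measures of anxiety and depression"; the sentence then adds, in brackets, that this happens before each new lesson. Section 6.3 says "During the trial all participants will be screened before completing each lesson when they complete brief measures of anxiety and depression".

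Section 5.2 names the instruments and their timing: "the GAD-7 and PHQ-9) will be administered at the beginning of each lesson to monitor anxiety and mood". Section 1.2 says the same.

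For Group 1, Section 5.2 says "This group will receive access to the entire program + automatic emails once the other groups have completed the program (week 9"). The flow table in Section 5.1 shows only waitlist status for this group from the pre-education stage in April until its questionnaires and interview in June.

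The response to a bad score is in Section 5.3, under During Completion of Questionnaires: "Any deterioration in mood or elevated distress will trigger protocols involving contacting the participant to discuss their emotional state", followed by a meeting to agree a management plan. That subsection lists when mood and anxiety questionnaires are completed: pre-education, before each lesson, post-education and the follow-ups. It lists no assessment during the wait. It separates the groups where it intends to, since the 12-month assessment is limited to Groups 2 to 4, but it makes no exception for Group 1 on screening.

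**The concern.** The safety statement covers all participants, while the schedule that delivers it covers only people taking lessons. During the wait Group 1 takes none. The contact procedure then has no score from this group to act on, although its members were recruited for elevated symptoms and are not yet receiving the program. Section 4.2 admits PHQ-9 totals up to 22.

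If a waitlisted participant worsens, nothing scheduled before week 9 would show it. An ethics committee reading Sections 5.3 and 6.3 would believe that a protection is in place which 50 people do not have. This is a matter of safety monitoring. It does not affect the estimation or testing of the treatment effect.

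**Working it through.** **Inputs**

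- Group sizes: 50 in Group 1, 350 in total (Sections 3.2 and 3.3).
- First full assessment: "At the beginning of the education program all participants will complete the outcome measure questionnaires" (Section 5.2). Take this as day 0.
- Second full assessment: post-education, 9 weeks after the program begins (Section 3.5). Section 1.2 agrees, placing it one week after an 8-week program.
- Lesson pace: five lessons over 8 weeks, and "participants are encouraged to complete one lesson every 10 days" (Section 5.2).
- Start of lessons in Group 1: week 9 (Sections 1.2 and 5.2).

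**Step 1: length of the wait.** The plan's own interval is reproduced: 8 + 1 = 9 weeks, and 9 × 7 = 63 days. If week 9 were read as beginning directly after the 8-week program, it would be 8 × 7 = 56 days.

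**Step 2: share affected.** 50 / 350 = 0.143, or 14%.

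**Step 3: scheduled PHQ-9 and GAD-7 scores after day 0 and before day 63.** Lesson 1 falls on day 0 with the pre-education questionnaires, so it is not counted as an extra screen.

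| Schedule | Screen days after baseline | Number | Gaps up to day 63 (days) | Longest gap (days) |
|---|---|---|---|---|
| Group 1 as planned | none | 0 | 63 | 63 |
| Groups 2 to 4, one lesson every 10 days | 10, 20, 30, 40 | 4 | 10, 10, 10, 10, 23 | 23 |
| Groups 2 to 4, slowest even pace within 8 weeks | 14, 28, 42, 56 | 4 | 14, 14, 14, 14, 7 | 14 |
| Group 1 with checks at weeks 3 and 6 | 21, 42 | 2 | 21, 21, 21 | 21 |

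On the 56-day reading, Group 1 still has no screens and a single gap of 56 days. With the two checks its gaps would be 21, 21 and 14, so the longest is still 21.

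**Step 4: can another provision supply the missing score?** These provisions cover Group 1 during the wait:

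- Entry screening excludes suicidal intent and people identified as at risk (Sections 4.2, 5.3 and 5.4). It is done once and cannot detect later worsening.
- Distress instructions and GP details are collected or given at application (Section 5.3). They rely on the participant acting, or on the team already being concerned.
- Emergency contacts appear in email footers and program materials (Section 5.3). Group 1 receives the program and its automatic emails only from week 9.
- "Members of the research team will meet at least 2 X weekly to discuss progress of each participant and of the overall trial" (Section 5.3). During the wait the team has no scheduled Group 1 score to discuss.
- Participants are invited to get in touch if they deteriorate (Section 6.3). This depends on the participant.

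None of these is a scheduled symptom measure.

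**The case against.** The strongest reply is that both sentences tie the screen to lessons, and Group 1 does take the lessons from week 9. Read literally, each member is eventually screened before each lesson, and neither sentence promises screening by calendar. That narrows the contradiction but does not remove it: the Section 5.3 sentence describes regular screening of everyone, and for the whole of the wait Group 1 gets none.

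The lesson link also has a rationale. Section 5.3 warns that practising the techniques can raise anxiety in the short term, so screening follows exposure to the program. This explains the design for Groups 2 to 4. It does not address worsening in people who have symptoms and are waiting.

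It can also be said that the contact procedure is not confined to scores, since distress learned of in another way would set it off. That is correct, and together with the safeguards listed above it reduces the gap. During the wait, though, such knowledge would come mainly from the participant.

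Two further points stand. The comparison with Groups 2 to 4 assumes that participants keep to a pace that is only advised. Someone in Group 2 or 3 who stops after lesson 1 also has no scheduled score until post-education; Group 4 has weekly calls. This is the same weakness in a lesson-linked rule, and it extends the point. Second, extra assessment and any contact it triggers would enter an arm meant to represent natural remission (Section 5.2). The protocol offers no figure for the size of that effect.

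**Conclusion.** The concern holds. As written, the safety rule does not reach 50 of 350 participants (14%) between the pre-education and week-9 questionnaires. They have no scheduled PHQ-9 or GAD-7 for 63 days, or 56 on the narrowest reading. Participants in Groups 2 to 4 who complete the lessons at an even pace within the 8 weeks have four.

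The result rests on the schedule in Sections 1.2, 3.5, 5.1 and 5.2, and on no waitlist assessment being scheduled elsewhere in the protocol. The comparison with Groups 2 to 4 depends on adherence to the lesson pace; the Group 1 count does not. The gap ends when Group 1 begins lessons. Because partial safeguards exist, this is a correction that should be made, not a fatal defect.

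**What to change.** 1. Send Group 1 the PHQ-9 and GAD-7 online during the wait, for example at weeks 3 and 6, and apply the contact procedure in Section 5.3 to the scores. The weeks are illustrative; investigators and the ethics committee may prefer others.
2. Correct the sentences in Sections 5.3 and 6.3 to say who is screened and when, for example: *Groups 2 to 4 complete the PHQ-9 and GAD-7 before each lesson. Group 1 completes them online at weeks 3 and 6 of the wait, and before each lesson once it starts the program at week 9.*

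The same calendar-based check could be sent to anyone in Groups 2 to 4 who has stopped starting lessons. The protocol gives no rate from which to cost that addition.

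For Group 1 the cost is two reworded sentences, 50 × 2 = 100 short questionnaire sets, and staff time to follow up any triggers. The measures and the response procedure are already in the protocol. The drawback is a little more contact in the control arm, which may slightly reduce its contrast with Groups 2 to 4. Those groups already complete the same two measures during the period, so the change brings the frequency of measurement closer across arms. If the sponsor declines the extra checks, the two sentences still need correcting, because they describe a protection that Group 1 does not have while waiting.
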